### Randomization and blinding

2.6

Randomization will be stratified by study center, with allocation ratio of 1:1 for each group. A random list of numbers will be generated using SAS software (version 9.2) by an independent statistician at the Good Clinical Practice (GCP) institute of the Xiyuan Hospital, who is not involved in the data collection or analysis. Research drugs will be numerically labeled and packaged according to the random numbers by the statistician of GCP institute. Participants will be allocated randomly into SMYZD group or control group according to the visit sequence. Participants, caregivers, investigators, data collectors and outcome assessors in this trial will remain blinded to allocated intervention until the study completion. Unblinding is permissible under the following circumstance:

(1)Participants develop another severe disease that need to be treated urgently;(2)Serious adverse event (SAE).

Withdrawal occurs when a participant's allocation or intervention is revealed.

### Intervention

2.7

All of the participants will undergo a 12-week treatment. All participants will receive GBEs (1 tablet, 3 times daily) as the basic treatment. One tablet of GBEs contains 19.2 mg of flavonol glucoside and 4.8 mg terpine lactone. GBEs used in this study are produced by Yangtze River Pharmaceutical (group) Co., Ltd. (Stata Food and Drug Administration Approval No. Z20027949).

The SMYZD group will receive SMYZD granule (1 bag, twice daily) plus GBEs. One bag (2.4 g) of SMYZD granule. The control group will receive mimetic granule of SMYZD (1 bag, twice daily) plus GBEs. Mimetic granule consists of dextrin (95%) and SMYZD granule (5%), which matches SMYZD granule with size, shape, taste and package.

In order to assess the medication adherence, the unused granules and tablets will be required to return to the research team and recorded on the CRF. SMYZD and mimetic granules are provided by the Beijing Tcmages Pharmaceutical Co., Ltd. (Beijing, China)

### Compliance, withdrawal and discontinuation

2.8

Several methods will be used to enhance the compliance and retention, including:

(1)all research drugs and scheduled assessments free of charge;(2)feedback to the caregivers or participants about the results of each assessment via telephone;(3)telephone reminder before each visit. The included participants can withdraw from the trial for any reason at any time.

Participants for the following reasons will be regarded as dropouts:

(1)loss to follow-up;(2)poor compliance;(3)voluntarily quit the project;(4)using prohibited medications;(5)urgency unblinding;(6)development of another severe disease that needs to be treated during the study.

Participants will be instructed to stop using the study drugs and visit their doctor when they are in the situation of any undesirable effect. We will compensate participants for trial-related harms. The reasons of withdrawal will be recorded in detail and be analyzed at the end of the trial.

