### Study design

2.1

This study is a multicenter, randomized, blind, controlled trial with a 1:1 allocation. The present protocol was registered at Chinese Clinical Trial registry (Number: ChiCTR1800017359) on July 25, 2018, and we design this protocol in accordance with the Standard Protocol Items: Recommendation for Interventional Trials 2013.

After a recruitment period and obtaining the signed informed consent from all the participants, eligible participants will be randomized to SMYZD group or control group, and receive treatment for 12 weeks, with a follow-up assessment at 24th week. A flowchart of the study is shown in Fig. 1. The evaluations and visits will be conducted according to the testing schedule as shown in Table 2.

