### Outcome measurements

2.10

The following outcomes will be assessed by trained assessors at specific visit timepoint, as shown in Table 2.

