#### Primary outcomes

2.10.1

1.The changes in cognitive function will be assessed by Alzheimer Disease Assessment Scale-cognitive subscale (ADAS-cog).^[35]^ The total score of ADAS-cog ranges from 0 to 70, and a higher score indicates more severe dysfunction.2.The neurological status will be evaluated by National Institute of Health stroke scale (NIHSS).^[36]^ The maximum score of NIHSS is 42, and a higher score represents more severe neurological deficit.

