#### Secondary outcomes

2.10.2

1.The Mini-Mental State Examination (MMSE) scale^[37]^ for assessing the extent of dementia.2.The Activities of Daily Living (ADL)^[38]^ score for rating quality of life.3.The changes in Traditional Chinese Medicine (TCM) symptoms will be assessed based on TCM syndrome scale score. The efficacy will be measured by a reduction (reduction = (before treatment score – after treatment score)/before treatment score × 100%) in the following scale: clinical cure: reduction ≧95%, markedly effective reduction ≧70%, effective: reduction ≧30%, invalid: reduction <30%.^[39]^4.Serum concentration of hypersensitive C-reactive protein (Hs-CRP), homocysteine (HCY) and neuron-specific enolase (NSE). The morning fasting venous blood will be obtained from participants. Separated serum will be stored at −80°C for further test.

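### Telephoning the results of each assessment to participants or caregivers can colour later ratings if outcomes differ by arm; efficacy scores should wait until after the week-24 assessment

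*Protocol article*

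**What the plan says.** Section 2.8 of the protocol article introduces its list with "Several methods will be used to enhance the compliance and retention, including". Item (2) is "feedback to the caregivers or participants about the results of each assessment via telephone". The other items are free drugs and assessments, and telephone reminders before visits. Item (2) does not say which results are meant, and it sets no time before which they are withheld.

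Four other parts of the article bear on this:

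- Section 2.6, on blinding: "Participants, caregivers, investigators, data collectors and outcome assessors in this trial will remain blinded to allocated intervention until the study completion".
- Section 2.1, on timing: participants "receive treatment for 12 weeks, with a follow-up assessment at 24th week".
- Section 2.10, on who rates: "The following outcomes will be assessed by trained assessors at specific visit timepoint". The timepoints are in Table 2, which is not shown. The primary outcomes are ADAS-cog and NIHSS. The secondary outcomes are MMSE, ADL, the TCM syndrome scale and three serum markers. On the TCM scale, section 2.10.2 states: "The changes in Traditional Chinese Medicine (TCM) symptoms will be assessed based on TCM syndrome scale score".
- Sections 2.8 and 2.13, on losses: poor compliance, voluntary withdrawal and use of prohibited medication all count as dropout. Missing values are to be multiply imputed.

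**The concern.** In a blinded trial, participants and caregivers are normally not told how the efficacy scores are moving while further ratings are still to come. Someone who has heard that the last result was better or worse brings that expectation to the next visit. Scales that draw on what the participant or caregiver reports are the most open to this. Disappointing news is also a reason to stop the granules, leave the trial or look for another cognitive treatment.

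Both arms are called in the same way, but the message follows the scores. If one arm improves more, it hears good news more often. A real difference could then be exaggerated on the softer scales, and losses could become related to outcome and so to arm. A measure adopted for retention could in that case work against it.

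**Working it through.** The document gives no figure for the effect of feedback, so the check is mainly one of setting the passages side by side. Arithmetic serves only to judge how strong a cue the feedback is.

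**1. Planning figures (section 2.5).** δ = 1.5, s = 3.5, α = 0.05, power 80%. The two-sided normal formula gives n = 2 × (1.960 + 0.842)² × 3.5² / 1.5² ≈ 85.5 per group. This is 86 rounded up, against 85 stated, and power at 85 is 79.8%. The plan's figure is reproduced to within one participant, so δ and s can be used below. The present point does not depend on the sample size.

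**2. Scope of the feedback.** Item (2) covers each assessment without exception. Section 2.10 has the outcomes measured at the scheduled visits. The natural reading is that efficacy results are included.

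**3. Which ratings can be affected.** Feedback can act only on what comes after it.

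| Efficacy assessed at | What could be affected |
|---|---|
| Baseline only, before week 12 | Nothing systematic by arm: baseline results do not depend on treatment |
| Week 12 | The week-24 ratings |
| A visit between baseline and week 12 | Adherence, dropout and the week-12 ratings as well |

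Section 2.1 places an assessment at week 24, after the 12 weeks of treatment. The second row therefore applies if efficacy is assessed at the end of treatment. The third row depends on Table 2.

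**4. Strength of the cue to allocation.** Take ADAS-cog change as normal with equal SD, and suppose the full planned effect is present. The standardised difference is d = 1.5/3.5 = 0.43, and d/2 = 0.214.

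- Best possible probability of guessing one's arm from one's own change: Φ(0.214) ≈ 0.58, against 0.50 by chance.
- Largest possible difference between arms in the proportion told good news, whatever the cut-off: 2 × Φ(0.214) − 1 ≈ 0.17, or 17 percentage points.

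The 58% also assumes that the guesser knows the best cut-off, which participants would not. It concerns ADAS-cog alone; the article gives no planning figures for the other scales.

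**5. No drug effect.** With d = 0 the two quantities become 0.50 and 0. The calls then carry no information about the arm, and no systematic difference arises while masking is intact.

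**The case against.** The strongest reply is that the article is condensed. What the caller says, and which scales are given at which visit, may be settled in the full protocol or in Table 2. This stands as far as adherence, dropout and the week-12 comparison are concerned: those effects need an efficacy assessment during treatment, and none is visible. It does not remove the point, because item (2) is a stated procedure with no limit on content or timing, and not something left unsaid.

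A second reply is that trained assessors do the rating, and that ADAS-cog and NIHSS rest on performance or examination. This also largely stands, and it is why the concern is mainly about ADL and TCM symptoms. That those two scales draw on participant or caregiver report is an assumption; the article does not say how they are completed.

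A third reply is that prohibited-drug users and those who leave are already counted as dropouts, that reasons for withdrawal are recorded and analysed, and that multiple imputation can absorb losses driven by recorded scores if those scores are in the imputation model. This is partly right for dropout. Imputation does not correct a rating that expectation has already shifted.

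Three stronger readings are tempting, and the document supports none of them:

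- *The feedback breaks the blind or contradicts section 2.6.* That section promises blinding to allocation. The calls disclose results, and step 4 shows these to be a weak cue.
- *The feedback could produce a positive result for an inactive treatment.* Step 5 shows that it would not while masking is intact.
- *A size can be attached, for instance 0.1 SD on ADAS-cog (0.1 × 3.5 = 0.35 points, or 0.35/1.5 = 23% of δ).* With at most 17 percentage points more good news in one arm, hearing good news would have to move the next score by 0.1/0.17 ≈ 0.59 SD, about 2.1 points. That exceeds the whole planned effect of 1.5 points, so such an illustration has no support.

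**Conclusion.** The concern holds in a limited form. As written, item (2) of section 2.8 allows efficacy results to reach participants and caregivers while ratings are still to come. If outcomes differ by arm, the content of the feedback differs too, and expectations can distort later ratings, mainly on the secondary ADL and TCM symptom scales. The exposure reaches week 24 if efficacy is assessed at week 12. It extends to adherence, dropout and the week-12 ratings only if efficacy is also assessed during treatment.

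The conclusion rests on two assumptions: that the results fed back include efficacy scores, which is the plain reading of an unrestricted text, and that ADL and TCM ratings depend at least partly on what participants or caregivers report. The size of the bias cannot be computed from the document. It is a cheap improvement of minor to moderate severity, not a flaw that invalidates the primary comparison.

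**What to change.** Reword item (2) of section 2.8 along these lines: *individual efficacy scores will be given to participants or caregivers only after the participant's week-24 assessment; during the study, safety-relevant results will be communicated as needed.* Keep the free drugs, free assessments and telephone reminders. If only laboratory or safety results were ever meant, a phrase saying so is enough.

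The cost is one line of protocol and an instruction to the sites. Sample size, endpoints and visit schedule are unchanged. The downside is that one retention incentive is delayed to the end of follow-up. Recruitment is already under way, so the change would apply to calls not yet made. Recording which participants had already received efficacy feedback would allow the week-24 results to be read in that light.

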### Statistical analysis

2.13

All the data will be analyzed by a statistician using SPSS 19.0 software (IBM Corp., Armonk, NY) in a blinded manner. Outcomes will be analyzed in accordance with the intention-to-treat (ITT) principle. Missing values will be handled by the multiple imputation method.^[40]^ Homogeneity of Baseline characteristics will be analyzed with *t* test for continuous variables and χ^2^ test for categorical variables, or with Wilcoxon Mann–Whitney test. Primary outcomes, and secondary outcomes will be analyzed by covariance with treatment groups as factors and baseline values as covariates. Mean difference will be used to illustrate the effect size.

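### The dropout and withdrawal rules in sections 2.6 and 2.8, read naturally as leaving the study, are inconsistent with the stated intention-to-treat principle and create avoidable missing outcomes

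*Protocol article*

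**What the plan says.** Section 2.8 (Compliance, withdrawal and discontinuation) states "Participants for the following reasons will be regarded as dropouts" and lists "1)loss to follow-up;(2)poor compliance;(3)voluntarily quit the project;(4)using prohibited medications;(5)urgency unblinding", followed by a sixth reason, "development of another severe disease that needs to be treated during the study".

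Section 2.6 (Randomization and blinding) permits unblinding for a severe illness needing urgent treatment or for a serious adverse event, and then states "Withdrawal occurs when a participant's allocation or intervention is revealed".

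Section 2.13 (Statistical analysis) states "Outcomes will be analyzed in accordance with the intention-to-treat (ITT) principle" and "Missing values will be handled by the multiple imputation method". It does not describe the imputation model and does not mention dropouts.

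Section 2.5 (Sample size calculation) allows for 15% discontinuation when it moves from 85 to 98 participants per group. Section 2.1 gives 12 weeks of treatment and an assessment at week 24.

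**The concern.** An intention-to-treat comparison depends on following randomised participants whether or not they keep to treatment. Poor compliance, use of a prohibited drug, unblinding and intercurrent illness are events after randomisation. They are not missing data, and none of them by itself prevents an ADAS-cog or NIHSS assessment. Section 2.8 nevertheless puts them on one list with true loss to follow-up.

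If a dropout is no longer assessed, the protocol itself produces the missing outcomes that section 2.13 then imputes. These events may also depend on prognosis and tolerability. Section 2.9 prohibits cholinesterase inhibitors and huperzine A, for example, which a worsening patient might start, and unblinding follows serious events. An imputation informed mainly by adherent participants then tends towards the effect that would be seen if everyone adhered, which is a different quantity from the intention-to-treat effect.

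This is a matter of trial conduct, not of analysis detail. A statistical analysis plan cannot recover scores that were never collected, and section 2.4 says recruitment is under way.

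**Working it through.** **Step 1. What dropout means in the text.** The article does not define the term for the analysis. Four features point towards leaving the study:

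- Section 2.8 uses withdrawal for a participant's exit from the trial.
- Directly after the dropout list, it says that reasons for withdrawal will be recorded, so dropouts are treated as withdrawals.
- The same section has separate wording for stopping the study drugs, and does not use it for the list.
- Section 2.5 enlarges the sample for discontinuation, which makes sense if those participants are expected to supply no outcome.

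Nothing in the text says that dropouts attend week 12 or week 24.

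**Step 2. The plan's own sample size.** Inputs from section 2.5: δ = 1.5, s = 3.5, α = 0.05 (taken as two-sided), power 80%.

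- n per group = 2 × (1.96 + 0.842)² × (3.5/1.5)² ≈ 85.5, so 86 when rounded up. The plan states 85, which is close enough.
- 85 × 1.15 = 97.75, so 98 as stated. (85/0.85 would give 100.)
- At 15% loss, 98 × 0.85 = 83.3 per group remain, with power 79.0%.

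The sample size therefore reproduces. It does not settle the point, but it supplies δ and the 15% used next.

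**Step 3. Illustration with equal rates.** Let d be the share affected in each arm and r the share of the effect they retain. If their outcomes are collected and used, the expected difference is 1.5 × [1 − d(1 − r)]. If they are imputed as though adherent, it is about 1.5. Neither d nor r is in the article, so the table gives a range.

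| d | r = 0 | 1.5 exceeds it by | r = 0.5 | 1.5 exceeds it by |
|---|---|---|---|---|
| 5% | 1.425 | 5% | 1.46 | 3% |
| 10% | 1.35 | 11% | 1.425 | 5% |
| 15% | 1.275 | 18% | 1.39 | 8% |
| 20% | 1.20 | 25% | 1.35 | 11% |

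The 15% row borrows the plan's discontinuation allowance. That allowance is not split by reason and also has to cover loss to follow-up and voluntary exit, so on the plan's own figure the avoidable share is likely to be smaller.

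**Step 4. Unequal rates.** Let p_a and p_c be the shares affected in the SMYZD and control arms, and let affected participants in either arm do k points worse. With no effect retained, the intention-to-treat difference is (1 − p_a) × 1.5 − p_a × k + p_c × k.

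- p_a = 0.20, p_c = 0.10, k = 2: 1.20 − 0.40 + 0.20 = 1.00. Imputing at 1.5 overstates the effect.
- p_a = 0.10, p_c = 0.20, k = 2: 1.35 − 0.20 + 0.40 = 1.55. Imputing at 1.5 slightly understates it.

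These rates and k are assumptions. Together they show that the sign is not determined.

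**The case against.** The strongest reply is that nothing here is a flat contradiction. The article does not say that visits stop for dropouts, that data already collected are thrown away, or that observed values are set to missing. Imputation is reserved for missing values, no dropout is excluded from the analysis, and no per-protocol set is defined. A dropout kept in the randomised arm, with observed data used and only the gaps imputed, would satisfy all three sections. The visit schedule and flowchart are not reproduced, and the full protocol may say more.

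Much of this stands. A reader might infer that real outcomes are replaced by imputed ones, but the text does not support that. A reader might also infer that the bias favours SMYZD. Step 4 shows that this depends on arm-specific rates that the article does not give: if worsening drives use of prohibited drugs and SMYZD works, more controls would be affected. The 18% figure is an upper case for the 15% row, since it assumes that all discontinuation is avoidable, that no effect is retained and that imputation makes no use of the scores of those who stop.

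The reply does not remove the point. Sections 2.6 and 2.8 state these rules affirmatively, so this is not a complaint about something an article leaves out. Their wording leads a site to stop assessing these participants.

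**Conclusion.** The point holds as a conditional inconsistency. Read in their natural sense, the dropout list in section 2.8 and the withdrawal sentence in section 2.6 conflict with the principle in section 2.13, because they make outcomes missing in people who could still be assessed. It does not extend to a claim that collected data are discarded or that the result is biased in a known direction.

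Under equal rates of 15%, the expected difference with complete follow-up would lie between 1.275 and about 1.39, against about 1.5 if imputed as though adherent. This is an overstatement of roughly 8% to 18%, smaller if fewer participants are affected. It rests on assumed rates, on zero or half of the effect being retained, and on an imputation model that the article does not describe. The change is worth making because it is cheap and because outcomes not collected cannot be recovered later.

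**What to change.** Reconcile sections 2.6, 2.8 and 2.13 as follows.

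- In sections 2.6 and 2.8, distinguish stopping study treatment from withdrawing from the study.
- Record poor compliance, prohibited medication, unblinding and intercurrent disease as events, with dates, instead of as dropout.
- Continue the scheduled week-12 and week-24 assessments for everyone who still consents.
- In section 2.13, state that all randomised participants are analysed with all observed outcomes, and that multiple imputation is used only for values that could not be obtained.
- Clarify the section 2.6 sentence so that unblinding does not by itself end outcome follow-up. It should not simply be deleted: it does not say whether withdrawal is from treatment or from the study, and deletion might remove a treatment-stopping rule. Any such rule stays as it is.

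The cost is protocol wording, an instruction to sites and some off-treatment visits within the existing schedule. The observed effect may be smaller. With 98 per group all followed and 15% affected, power would be 72.2% (no effect retained) or 79.2% (half retained), compared with 79.0% at δ = 1.5 if those outcomes were simply lost. The lower figures reflect the smaller effect that the intention-to-treat comparison is meant to estimate.

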### Prohibited concomitant medications

2.9

To promote comparability of study groups, drugs that recommended in the 2011 Chinese guidelines for the diagnosis and management of cognitive impairment and dementia (V): dementia therapy^[34]^ are prohibited, including:

1.cholinesterase inhibitors;2.excitatory amino acid receptor antagonists;3.antipsychotic medications;4.long-acting benzodiazepines;5.anti-depressive drugs;6.anxiolytic drugs;7.huperzine A;8.drugs that regulate free radical metabolism;9.Chinese medicines (including decoctions, herbal extracts, and Chinese patent medicines) that improve cognitive function.

Short-acting benzodiazepines will be restricted to use (less than 2 times per week, and it will be prohibited in the 72 hours before assessments). Other drugs that do not explicit any known actions on the central nervous system are permitted. The name, dosing period, frequency, dosing amounts of these drugs will be recorded on the CRF.

